### Cost-effectiveness and cost-benefit analyses

The cost-effectiveness analysis includes the percentage of antibiotic prescribing as outcome. A cost-benefit analysis, in which the reduction in antibiotic prescribing will be expressed in monetary terms, will also be performed. Missing data will be imputed in the cost-effectiveness analysis using multiple imputation techniques. Fully Conditional Specification and Predictive Mean Matching will be used to create ten complete data sets. Pooled estimates will be calculated according to Rubin’s rules [46]. We will calculate the mean differences for total and disaggregated costs and perform seemingly unrelated regression analyses, correcting for baseline characteristics and taking into account possible correlations between costs and effects. An incremental cost-effectiveness ratio will be calculated, with a corresponding cost-effectiveness plane. The cost difference and incremental cost-effectiveness ratio will be Bootstrapped with 5000 replications. The probability of cost-effectiveness at different values of willingness-to-pay will be estimated and presented on a cost-effectiveness acceptability curve. We will conduct sensitivity analyses on uncertain parameters to evaluate the robustness of the results.

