## Methods/design

### Study design and population

The UPCARE study design is a cluster RCT, with randomization at NH organization level. This randomization level was chosen because of our pragmatic trial design and in order to avoid spill-over effects. Data collection starts September 2018 and will, based on calculations of expected inclusion rate, last approximately 1.5 year. Eleven NH organizations across the Netherlands will participate in the study. A simple randomization procedure using Microsoft Office Excel 2016 software will be performed by the research team to allocate participating organizations to either the control or intervention group (1:1).

Dutch NHs typically have three types of specialized wards: somatic wards that accommodate physically disabled residents, psychogeriatric wards that accommodate residents with dementia, and geriatric rehabilitation wards. NH admission to one of these wards and the required level of care is determined by a standardized assessment performed by a government agency (“Centrum Indicatiestelling Zorg” (CIZ)). Unique to Dutch NHs is the employment of specialized ‘elderly care physicians’. Other NH prescribers may include physicians with other specializations or general medical training, elderly care physicians in training, and nurse practitioners. Dutch NH medical care typically excludes the use of intravenous drugs, and hospital referrals are limited [40, 41].

The study population comprises NH residents from psychogeriatric, geriatric rehabilitation, or somatic wards, who are newly diagnosed with a ‘suspected LRTI’. Patients are excluded if they receive palliative/terminal care with a restrictive antibiotic policy, if they do not wish to be treated with antibiotics, if they are using antibiotics (currently or in the past week), or if they have an infection other than the suspected LRTI (currently or in the past week).

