### Sample size calculation

Based on previous study data [40], we expect 15% less antibiotic prescriptions in the intervention group compared to the control group (i.e. 80% respectively 95%). In order to detect this difference, with 80% power and at a 5% significance level, 146 cases would be required. If we randomize eleven NH organizations with an average number of 400 residents (cluster size) and with an intracluster correlation coefficient of 0.06, the required number of cases is 671 [42].

The expected incidence rate of suspected LRTI is 3.5 cases per 1.000 resident-care weeks in NHs [2]. Based on previous study data, we expect that at most 10% of cases will not meet inclusion criteria and that 75% of eligible cases provide informed consent for study participation. This means that of all LRTI cases, approximately 70% can be included in the study, which translates into an expected 2.4 suspected LRTI per 1.000 resident-care weeks.

ln order to include 671 cases of LRTI in eleven organizations with an average number of 400 residents the study period totals to 1.5 year, with a small margin for potential suboptimal inclusion.

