### Data analysis

The primary analysis will be intention-to-treat and will assess the effect of CRP POCT on antibiotic prescribing for suspected LRTI at index consultation. A three-level logistic regression model will be used to account for variation at the NH/physician/patient level. If there is no indication of random effects at the physician level, the model will be reduced to a two-level model. Multilevel regression modeling will similarly be used to compare secondary study outcomes between the two groups (linear or logistic, as appropriate). A second-order penalized quasi-likelihood estimation procedure will be applied.

Pharmacy data on total antibiotic prescribing will be explored descriptively, in order to describe the potential impact of adjusted antibiotic prescribing for LRTI on total antibiotic prescribing within intervention NHs, compared to control NHs. Total antibiotic prescriptions will be expressed per 1000 residents per year.

Data of patients in the intervention group will be used to explore potential relations between CRP POCT values and; 1) signs/symptoms in NH patients with suspected LRTI, and 2) antibiotic treatment. Multiple linear or logistic (as appropriate) regression modeling will be performed.

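### As written, the economic evaluation names a single-level regression and no allowance for clustering, although nursing home organisations are randomised

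*Protocol article*

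**What the plan says.** Under Study design and population the protocol article states: "The UPCARE study design is a cluster RCT, with randomization at NH organization level". It adds: "Eleven NH organizations across the Netherlands will participate in the study". Sample size calculation inflates the number of cases with an intracluster correlation of 0.06. Data analysis uses a three-level logistic model for antibiotic prescribing, reducible to two levels, and multilevel models for the secondary outcomes.

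The section Cost-effectiveness and cost-benefit analyses sets out a separate method. Its effect measure is the percentage of antibiotic prescribing. The regression step is to "perform seemingly unrelated regression analyses, correcting for baseline characteristics and taking into account possible correlations between costs and effects". On resampling it says: "The cost difference and incremental cost-effectiveness ratio will be Bootstrapped with 5000 replications". On missing data it says: "Fully Conditional Specification and Predictive Mean Matching will be used to create ten complete data sets". Rubin's rules pool the results, and an acceptability curve is to be presented. Organisation is not mentioned in any of these steps.

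The multilevel sentence in Data analysis does not fill the gap. It covers the secondary outcomes, and the Outcomes section describes costs in a separate paragraph outside that list.

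**The concern.** Seemingly unrelated regression links the error terms of the cost and effect equations within a patient. In its standard form it has no term for patients who share an organisation. The section says which dependence it will handle, the one between costs and effects, and that is not the dependence created by the randomisation.

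The treatment contrast lies wholly between organisations, so its uncertainty is driven largely by variation between them. A patient-level analysis leaves out that variation. The article would then report the same antibiotic difference twice: once with clustering as the primary result, and once, apparently far more precisely, on the effect axis of the cost-effectiveness plane.

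Cost-effectiveness is a stated aim. The article also says that the new guideline does not specifically advise the point-of-care test because evidence on its effectiveness and cost-effectiveness is insufficient. An overconfident acceptability curve would bear directly on that question.

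**Working it through.** **Inputs from the documents.** 95% v 80% prescribing, 80% power, 5% significance, 146 cases without clustering, ICC 0.06, eleven organisations and 671 cases (Sample size calculation); randomisation by organisation, 1:1 (Study design and population). **Assumed:** equal cluster sizes, two-sided testing, and any ICC for costs.

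**1. Reproduce the plan's figures.**
- Unclustered, unpooled variance: (1.96 + 0.8416)² × (0.95×0.05 + 0.80×0.20) / 0.15² = 7.849 × 0.2075 / 0.0225 = 72.4. Rounded up this is 73 per arm, or 146 in total, as stated.
- Cases per organisation: 671 / 11 = 61.
- Design effect: 1 + (61 − 1) × 0.06 = 4.6. Then 146 × 4.6 = 671.6, which matches the stated 671.
- The article labels the 400 residents as the cluster size. With 400 the design effect would be 24.94 and the total 3641, so the stated 671 rests on 61 cases per organisation. That figure is used below.

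**2. Effect difference, if analysed at patient level.**
- Ratio of the correct to the patient-level standard error: √4.6 = 2.14.
- Real coverage of a nominal 95% interval: 2Φ(1.96 / 2.14) − 1 = 64%.
- Effective number of cases: 671 / 4.6 = 146.
- In percentage points, with about 335.5 cases per arm: patient-level SE = √(0.2075 / 335.5) = 2.5 points, a half-width of about 4.9 points. With clustering the SE is 2.5 × 2.14 = 5.3 points, a half-width of about 10.5 points. With a t quantile on 9 df (11 clusters − 2), the ratio of widths is 2.48 and the half-width about 12.1 points.
- A simulation with a continuous outcome (11 clusters of 61, 5 v 6, ICC 0.06, 4000 runs) gave 64% coverage for the patient-level interval and 95% for a t interval on cluster means.

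**3. Cost difference, if analysed at patient level.** The documents give no ICC for costs, so a range is shown.

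| Assumed cost ICC | Design effect | SE too small by | Coverage of nominal 95% |
|---|---|---|---|
| 0.01 | 1.6 | 1.26 | 88% |
| 0.03 | 2.8 | 1.67 | 76% |
| 0.05 | 4.0 | 2.00 | 67% |

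**4. Acceptability curve.** This combines both axes, so its error depends on the unknown cost ICC. As an illustration only: if net benefit had an ICC of 0.06, a patient-level probability of 0.95 would become Φ(1.645 / 2.14) = 0.78.

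**5. Imputation.** No figure can be given. The effect of leaving out organisation depends on the amount of missing data, which the article does not state.

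**The case against.** The strongest reply is that this is an inference from silence. The article does not say that patients are resampled, that imputation is at patient level, or which standard errors accompany the regression. It is a condensed publication, and such details often sit in the full protocol or analysis plan. It plainly recognises clustering elsewhere. Seemingly unrelated regression combined with a bootstrap that resamples organisations would fit the existing wording.

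Much of this stands. A reader might infer that the plan commits to patient-level resampling and imputation, or that every economic interval will be far too narrow. The documents support neither reading. The resampling unit and imputation level are unstated. The factor of 2.14 concerns the effect difference alone, and only under a patient-level analysis. At a cost ICC of 0.01 the loss on the cost side is moderate. Baseline adjustment may also change the residual ICC.

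A reader might also extend the point to the models relating CRP values to symptoms and treatment, for which the article says: "Multiple linear or logistic (as appropriate) regression modeling will be performed". That does not follow. Those models are exploratory and use the intervention group only. Their predictors vary between patients within organisations, so the design effect for an organisation-level treatment does not apply to them.

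What does not stand is that the whole matter is omitted detail. The section names its estimator, the dependence that estimator handles, the number of imputations and the number of bootstrap replications. The named estimator is single-level in standard form and sits immediately after a section that chose multilevel models for the same endpoint.

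**Conclusion.** The concern holds in conditional form. The economic section names a single-level estimator and provides for clustering in none of its regression, bootstrap or imputation steps. Whether the reported uncertainty will be wrong depends on how these steps are carried out.

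If they are carried out at patient level, the understatement on the effect side is large and rests on the plan's own ICC together with equal clusters of 61 cases. On the cost side it ranges from moderate to large over the assumed ICCs. The plane and the curve would be too certain, but by how much cannot be fixed from the documents. The primary and secondary clinical comparisons are unaffected, because they are already multilevel.

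**What to change.** - **Regression.** Replace the single-level regression with a bivariate multilevel model for costs and effects, with a random intercept for the randomised organisation and a small-sample correction for eleven clusters. Cluster-robust seemingly unrelated regression with such a correction is an acceptable alternative.
- **Bootstrap.** State the resampling unit and make it respect organisations within arm. Acknowledge that any cluster bootstrap is weak with five or six organisations per arm, so it should not be the only safeguard.
- **Imputation.** Include organisation in the imputation model, so that it matches the clustered analysis.

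The cost is some rewording of the plan, a little more analysis work, and wider intervals with a flatter acceptability curve. Data collection and sample size do not change.

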## Discussion

This protocol paper describes the design of a cluster RCT to assess the effect of CRP POCT on antibiotic prescribing for LRTI in NHs. This is, to our best knowledge, the first large RCT to evaluate this topic in the NH setting. With this study, we aim to contribute to antibiotic stewardship efforts in the NH setting.

### Reflection on study design

#### Study population

We use broad inclusion criteria for the study population, for example we include patients from somatic, geriatric rehabilitation, and psychogeriatric wards. Research in the psychogeriatric population may be challenging, for instance with regard to obtaining informed consent. However, results of this study are especially important for this population as quick diagnosis and treatment initiation can be challenging (i.e. difficult clinical assessment) but essential given the vulnerability of this population [5, 16, 17, 21].

#### Control group

During the study we remain vigilant towards potential post-randomization recruitment bias: the control group might gradually or throughout the trial be less inclined to recruit patients, given the absence of the intervention [14, 20]. We anticipate the need for incentives especially in the control group during the trial. Another phenomenon that may arise in the control group is the Hawthorne effect, that is, a shift towards more rational antibiotic prescribing because of the physician’s awareness of being observed [29, 47].

#### Data collection

An anticipated strength of the study is the data collection method. The integration of the research tool in the electronic patient file ensures that data are collected in an efficient way. In addition, the use of automatic reminders and other technical support reduce the risk of missing data.

#### Informed consent procedure

Reasons for exercising a deferred consent procedure stem from parallels seen in emergency research to this study, which we consider in emergency situations and in case the representative is unavailable [48, 49].

In case of certain emergency situations, CRP POCT could directly benefit patient care. For instance, CRP POCT might provide the physician with valuable information for the differential diagnosis between LRTI and congestive heart failure. Another consideration in asking consent during an emergency situation is that it might conflict with sufficient comprehension of study participation and with the principle of “evidencing a choice” [49].

Another situation that warrants deferred consent arises when the representative of an incapacitated resident is not readily available at index consultation. In that case, a requirement for prior consent could interfere with the time span within which CRP POCT is still worthwhile. Consequently, this subpopulation is unnecessarily disadvantaged in diagnostic possibilities - assuming the added value of CRP POCT that is seen in general practice and considering the higher burden of venipuncture compared to finger prick if CRP would instead be determined by laboratory assessment. Also, selection bias may appear if this subpopulation is more often excluded from the study because of difficulty in obtaining consent.

The alternative to ask consent pre-emptively was considered, however, this would require burdening a disproportionate number of residents with the question of consent, compared to those becoming eligible for participation. Moreover, as the period between consent and study participation could be lengthy the resident may not remember the choice for and extent of study participation.

### Reflection on study context

#### Antibiotic stewardship in NHs

In the Netherlands in recent years, antimicrobial resistance in different settings such as NHs has gained a more prominent place on the research and public health agenda. Antibiotic stewardship efforts are widely supported and developed for the NH setting by different parties. During the UPCARE study, it is important to monitor such activities as they might influence the primary outcome.

#### LRTI guideline for the NH setting

Around the start of data collection, a LRTI guideline was published for the NH setting by the Dutch Association of Elderly Care Physicians and Social Geriatricians. In this guideline, physicians are instructed to assess the CRP-level for patients who are moderately ill and who have certain clinical signs and symptoms that do not indicate LRTI unambiguously. In the guideline, CRP POCT is not specifically advised for CRP-measurement, as evidence for its (cost-) effectiveness is currently insufficient. With the UPCARE study we aim to address this knowledge gap.

#### Pragmatic trial design

We advise physicians and nurses in the intervention group on the possible use of CRP POCT and support them in this matter, but we do not use strict protocols on the use and interpretation of CRP POCT; physicians remain in charge of their diagnostic work-up and management decisions. This pragmatic design enables us to observe an effect that reflects daily practice. This increases the chance that our findings will be generalizable and widely applicable [14, 20]. A potential pitfall of this approach is that the medical training session and other study preparations might not sufficiently incite behavioural change. Essential to the potentiality of a positive effect of the intervention is that physicians learn to trust CRP POCT findings and subsequently use these findings to adjust management when appropriate [20]. However, the use of CRP-measurements in general is not new and results from general practice are encouraging. Furthermore, all NHs will have a run-in period before study commencement to familiarise themselves with the use of CRP POCT (device and results). We will perform a process evaluation to explore the extent to which the intervention has been successfully implemented and used.

## Conclusion

This is the first large RCT to evaluate CRP POCT for suspected LRTI in the NH setting. The broad inclusion criteria and pragmatic study design add to the applicability and generalizability of the study results. With this study we aim to contribute to antibiotic stewardship efforts in the NH setting.

## Data Availability

The datasets generated and/or analysed during the current study will be deposited in the repository DANS (EASY) after publication of the research results, within a maximum of 9 months post study termination. The dataset(s) involved will be anonymised/pseudonymised and can be accessed under restrictions.

## Abbreviations

CRF: Case Record Form
CRP POCT: C-Reactive Protein Point-Of-Care Test(ing)
LRTI: Lower Respiratory Tract Infection
NH: Nursing Home
NHAP: Nursing Home-Acquired Pneumonia
RCT: Randomized Controlled Trial
